### Sample size calculation

The OED is known to be independent of haematoma size, with a normal distribution. Based on the available preclinical and clinical data we assume an OED of 0.60 (SD 0.25) at day seven in the standard care group and estimate a reduction of OED from 0.60 to 0.40 (SD 0.25) in the anakinra treated group (high and low dose groups combined).^
30
^ With a group size ratio of 1:2 for control versus treatment, a power of 0.80, and an alpha of 0.05, a sample size of 19 patients in the control group, and of 39 in the intervention group is required. Assuming a 25% drop-out rate due to the severity of ICH, the final sample size is 25 patients for the control group and 50 patients for the intervention group, resulting in a total sample size of 75 patients for this trial.

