### Statistical methods

The primary analysis of this trial will be conducted under the principle of intention-to-treat. Baseline characteristics of the patients included in each treatment group will be reported and tabulated to demonstrate group comparability. For the primary analysis, we will use a two-sided independent t-test to determine a mean difference and 95% CI between the OED at MRI on day 7 ± 1 of the two anakinra treatment groups combined and the standard care group. In an exploratory analysis, we will determine whether a difference in OED exists between the high dose and low dose anakinra group, again using a two-sided independent *t*-test.

Safety analyses will include all SAEs and AESIs up to 90 days after randomisation. To determine the safety profile of anakinra between the three treatment arms, we will compare the number of AESIs and urgent medical reasons for study withdrawal between the three treatment arms in 2 × 3 tables, tested by the Fisher exact probability test. To assess BBB disruption, difference in the K^trans^ between the three treatment groups will be analysed with ANOVA.

To determine the effect of anakinra on the time-dependent profile of serum inflammatory markers, we will use a linear mixed model to assess the effect of anakinra dosage on the area under the curve for these metabolites compared to standard care. The effect of the treatment on the distribution of the mRS at 90 ± 7 days will be analysed using ordinal logistic regression yielding common odds ratio’s with corresponding 95% CI. We will use a two-sided independent t-test to determine a mean difference and 95% CI between the Barthel Index of the two anakinra treatment groups combined versus the standard medical management group.

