A potential limitation of our study is the relatively limited sample size. The high mortality rate after ICH might lead to a substantial drop-out of study participant that are not able to undergo a MRI examination at 7 ± 1 days. Although our sample size would allow for a 25% drop-out, this might be higher resulting in decreased statistical power. Moreover, the estimated effect size is based on preclinical data which might not translate to a human study. Using OED as our metric for PHO in our primary outcome analysis aims to mitigate the required sample size, as it is not affected by haematoma volume and thus strongly reduces the required sample size in comparison with using absolute or relative PHO.^
27
^

One other randomised phase II study has investigated anakinra to reduce PHO in patients with ICH (BLOC-ICH).^
23
^ In this placebo-controlled trial, patients with spontaneous supratentorial ICH were randomised to receive either 100 mg of anakinra subcutaneously twice daily during the 72 h after ICH onset, or placebo. Primary outcome was OED on CT imaging obtained at day 3 after symptom onset. Secondary outcomes included serum inflammation markers and functional outcome at 3 months. Patient recruitment was severely impacted by the COVID-19 pandemic and the trial had to be ceased prematurely after inclusion of 25 of the intended 80 participants. Although this trial provides preliminary data on the safety and feasibility of anakinra in acute ICH patients, it lacked statistical power to determine the effect of anakinra on perihaematomal oedema formation. We will collaborate with the investigators of BLOC-ICH to combine data into an individual patient data meta-analysis of patients treated with anakinra after ICH once the ACTION trial has been completed.

In conclusion, the ACTION trial has the potential to offer valuable insights into the role of neuroinflammation in the development of secondary brain injury after ICH, and whether this can be therapeutically modulated. Moreover, it will help determine the feasibility and design of future phase III trials of immunomodulatory therapies in patients with ICH.

## Appendix 1

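### The 75 randomised patients do not cover a 25% drop-out from the stated 19 and 39; they cover about 22%, and t-test power at 25% is about 0.79 (minor)

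*Protocol article*

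**What the plan says.** All the inputs are in the protocol article.

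- **Effect and spread** (Sample size calculation): "we assume an OED of 0.60 (SD 0.25) at day seven in the standard care group", and the investigators "estimate a reduction of OED from 0.60 to 0.40 (SD 0.25) in the anakinra treated group", high- and low-dose groups combined.
- **Design values** (same section): "With a group size ratio of 1:2 for control versus treatment, a power of 0.80, and an alpha of 0.05".
- **Test** (Statistical methods): "For the primary analysis, we will use a two-sided independent t-test", comparing the combined anakinra groups with standard care.
- **Requirement before drop-out** (Sample size calculation): "a sample size of 19 patients in the control group, and of 39 in the intervention group is required".
- **Inflation** (same section): a loss of one patient in four is assumed because the disease is severe, and the article concludes that "the final sample size is 25 patients for the control group and 50 patients for the intervention group", which makes 75 in all.
- **Repeat of the allowance** (Discussion, paragraph on limitations): "Although our sample size would allow for a 25% drop-out", followed by a warning that the true rate may be higher and power lower.

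**The concern.** A drop-out allowance should leave the required number of evaluable patients once the assumed fraction has been lost. Here the requirement, the drop-out rate and the final size stand side by side in one section, and the last does not follow from the first two.

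The primary outcome is measured on one MRI at day 7, so a patient without that scan contributes nothing to a complete-case t-test. The Discussion itself names drop-out as the route by which power may be lost. Readers of the finished trial will probably use 25% as the benchmark for whether planned power was kept. A realised drop-out of 23% to 25% would then be read as within the allowance, although the plan's own count of evaluable patients had already been missed.

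**Working it through.** **1. Reproduce the requirement.** The difference is 0.60 − 0.40 = 0.20 cm with SD 0.25, so the standardised difference is 0.20/0.25 = 0.8. For a two-sided t-test at 0.05, the noncentrality is 0.8/√(1/n₁ + 1/n₂) with n₁ + n₂ − 2 degrees of freedom.

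| Control / anakinra | Noncentral-t power |
|---|---|
| 19 / 38 | 0.799 |
| 19 / 39 | 0.802 |

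19/38 falls just short of 0.80 and 19/39 reaches it. The stated pair is therefore reproduced exactly as a t-test requirement, and this step of the plan is correct.

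**2. Apply the 25% drop-out.** The number to randomise is n/(1 − 0.25).

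- Control: 19/0.75 = 25.33, rounded up to 26.
- Anakinra: 39/0.75 = 52 exactly.
- Total: 26 + 52 = 78, or 26 per arm at 1:1:1.

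The plan gives 25 + 50 = 75, three fewer.

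**3. Check in the other direction.** Expected evaluable patients after 25% loss:

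- Control: 25 × 0.75 = 18.75, against 19 required.
- Anakinra: 50 × 0.75 = 37.5, against 39 required.
- Total: 56.25, against 58.

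**4. Drop-out that 75 does cover while keeping 19 and 39.**

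- Control: 1 − 19/25 = 24.0%.
- Anakinra: 1 − 39/50 = 22.0%.
- Overall: 1 − 58/75 = 22.7%.

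**5. Cost in power for the planned t-test** (difference 0.20, SD 0.25):

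| Evaluable patients | Power |
|---|---|
| 19 / 39, as stated | 0.802 |
| 18.75 / 37.5, expected at 25% drop-out | 0.793 |
| Averaged over independent binomial 25% losses from 25 / 50 | 0.789 |

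With the same drop-out in both groups, power from 25/50 is exactly 0.80 at a drop-out of 23.8%.

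**6. Routes that could lead to 75.** The article does not say how it got from 19 and 39 to 25 and 50, so both of these are inferences.

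- *Unrounded normal approximation.* n₁ = 1.5 × [0.25 × (1.960 + 0.842)/0.20]² = 18.40 and n₂ = 36.79. Dividing by 0.75 gives 24.53 and 49.06, which round up to 25 and 50. Normal-approximation power at 18.75/37.5 is 0.807.
- *Multiplying by 1.25 instead of dividing by 0.75.* 19 × 1.25 = 23.75 and 39 × 1.25 = 48.75, which round up to 24 and 49. Raising to three equal arms gives 25 each.

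**The case against.** The best defence is that 75 patients, 25% drop-out and 80% power do agree under a common formula, as the first route in step 6 shows. That is true, and it rules out the stronger reading that these three figures are irreconcilable under any method. They disagree for the planned t-test and with the stated 19 and 39. The defence does not make the text right, because the article names a t-test and its 19/39 is the t-test requirement. The normal approximation would have given 19 and 37 after rounding up, or 38 if the control figure is doubled.

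A second defence is rounding. It could excuse the control group (25.33 to 25) but not the anakinra group, where 39/0.75 is exactly 52 and the plan has 50.

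A third is that the effect is negligible, and most of this stands. The shortfall is about 1 point of power, and to one decimal place power is still 0.8. Uncertainty in the inputs matters more: an SD of 0.26 instead of 0.25 lowers power at 19/39 from 0.802 to 0.771. The Discussion also already warns that the effect size rests on preclinical data and that drop-out may exceed the allowance.

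A reader might round both groups down to 18 and 37 and quote a power of 0.780. That overstates the loss: 55 of 75 evaluable is a drop-out of 26.7%, not 25%. At 19/37, a total of 56, power is 0.795.

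**Conclusion.** The point holds as a minor correction. Given the stated requirement, the 25% allowance is wrong as written in the Sample size calculation and again in the Discussion. The real tolerance is 22.0% in the anakinra group, 24.0% in the control group and 22.7% overall. Power at 25% drop-out is about 0.79.

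This rests on the article's own effect, SD, alpha and two-sided t-test, and on reading drop-out as absence of a usable day-7 MRI at the same rate in both groups.

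A reader might infer that the trial is underpowered or needs to enrol more patients. The documents do not support that: the gap is three randomised patients and about 1 point of power, and neither the design nor the primary analysis is affected.

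**What to change.** Keep 75 patients. In the Sample size calculation, replace the claim that 25 and 50 cover a 25% drop-out with one of two statements:

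- 75 randomised patients retain the required 19 and 39 up to a drop-out of about 22%; or
- at 25% drop-out, the planned two-sided t-test has power of about 0.79 under the stated assumptions.

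Amend the Discussion sentence on the 25% allowance to match whichever is chosen. If 75 was in fact derived from the unrounded normal approximation, say so, and do not present it as following from 19 and 39.

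The cost is one sentence in each of two places and a slightly less favourable stated tolerance or power. Recruitment, design and analysis are unchanged.

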### Trial status

Patient recruitment started in July 2022 and is expected to finish in the last quarter of 2024.

## Discussion

ACTION is a multicentre randomised phase II trial studying the effect of anakinra on PHO development in patients with spontaneous supratentorial ICH. The primary aim of this trial is to establish whether administration of anakinra can reduce PHO as measured by the OED. In addition, we will assess the safety profile of anakinra in patients with ICH, and whether use of anakinra affects serum inflammation markers, BBB integrity, and clinical outcome during follow-up.

Experimental and clinical evidence indicates that targeting IL-1β is a promising therapeutic strategy in stroke patients. For this purpose, anakinra is an attractive option, as it is a highly selective IL-1ra that penetrates into the central nervous system and has an excellent safety profile. However, the optimal dosage of anakinra in patients with ICH is still unclear. The two clinical trials that have investigated the use of anakinra in patients with acute stroke have studied different dose regimes. The first trial used a high-dose regime consisting of a 100 mg loading dose followed by continuous infusion of 2 mg/kg/h for 3 days,^
21
^ whereas the second trial used a low-dose anakinra regime of 100 mg twice daily for 3 days.^
22
^ Anakinra was found to be safe and well tolerated in both trials and markedly attenuated the levels of circulating inflammatory molecules such as CRP and IL-6 levels.

Under physiological conditions approximately 1% of anakinra crosses the BBB,^
25
^ which would imply that administration of a high dosage of anakinra is probably needed for clinically relevant levels in the brain. However, after ICH, higher concentrations of anakinra are expected to enter the brain parenchyma adjacent to the haematoma since the BBB integrity in the perihaematomal region is compromised. This might allow a lower dose regime with improved patient tolerance at significant lower cost. The three-armed design of ACTION may help to design future phase III trials by estimation of effect sizes and comparison of the high intravenous and low subcutaneous anakinra dosage. The primary analysis will provide evidence as to whether anakinra can influence the development of secondary brain injury, while secondary analysis will assist determining the required dose regimen. In addition, we use advanced DCE-MRI to quantify BBB disruption in the perihaematomal region as an indirect marker of neuroinflammation.

A potential limitation of our study is the relatively limited sample size. The high mortality rate after ICH might lead to a substantial drop-out of study participant that are not able to undergo a MRI examination at 7 ± 1 days. Although our sample size would allow for a 25% drop-out, this might be higher resulting in decreased statistical power. Moreover, the estimated effect size is based on preclinical data which might not translate to a human study. Using OED as our metric for PHO in our primary outcome analysis aims to mitigate the required sample size, as it is not affected by haematoma volume and thus strongly reduces the required sample size in comparison with using absolute or relative PHO.^
27
^

One other randomised phase II study has investigated anakinra to reduce PHO in patients with ICH (BLOC-ICH).^
23
^ In this placebo-controlled trial, patients with spontaneous supratentorial ICH were randomised to receive either 100 mg of anakinra subcutaneously twice daily during the 72 h after ICH onset, or placebo. Primary outcome was OED on CT imaging obtained at day 3 after symptom onset. Secondary outcomes included serum inflammation markers and functional outcome at 3 months. Patient recruitment was severely impacted by the COVID-19 pandemic and the trial had to be ceased prematurely after inclusion of 25 of the intended 80 participants. Although this trial provides preliminary data on the safety and feasibility of anakinra in acute ICH patients, it lacked statistical power to determine the effect of anakinra on perihaematomal oedema formation. We will collaborate with the investigators of BLOC-ICH to combine data into an individual patient data meta-analysis of patients treated with anakinra after ICH once the ACTION trial has been completed.

In conclusion, the ACTION trial has the potential to offer valuable insights into the role of neuroinflammation in the development of secondary brain injury after ICH, and whether this can be therapeutically modulated. Moreover, it will help determine the feasibility and design of future phase III trials of immunomodulatory therapies in patients with ICH.

## Appendix 1

